**Effect of a new rocuronium formulation in reducing injection pain**

1. Objectives and significance

Objectives

We will investigate whether the injection pain associated with induction of anesthesia is milder when using a new rocuronium formulation than when using Eslax. The primary outcome is whether or not there is a withdrawal response of the upper limb after injection of the drugs. The secondary outcomes are the magnitude of the withdrawal response and changes in blood pressure and heart rate before and after injection of the drugs.

Significance

Rocuronium is a non-depolarizing muscle relaxant that is widely used during the induction of general anesthesia due to its superior muscle relaxant effect and its high level of safety owing to the existence of a specific antagonist.

However, the rocuronium formulation currently sold in Japan (generic name: Eslax) causes transient vascular irritation at the time of intravenous injection. Since this irritation is transient and rocuronium is injected after the onset of sleep, it is rare for the patient to feel the irritation at the time of injection as pain or for vascular pain to occur after the conclusion of surgery. However, there are instances when the irritation can be problematic in terms of anesthesia management, such as when the patient cannot be kept still due to a reflexive withdrawal response or when heart rate and blood pressure increase as a consequence. Therefore, development and clinical application of a rocuronium formulation that is less irritating on injection could improve the quality and safety of general anesthesia.

1. Basis and background of scientific rationale

The new rocuronium formulation developed by Maruishi Pharmaceutical Co., Ltd. (new drug) has been shown in animal experiments to be less irritating to the blood vessel during intravenous injection than Eslax. This effect was achieved by switching the buffer contained in the injection solvent from sodium acetate to glycine. This study is being conducted because there have been no studies on whether the new drug reduces the injection pain of rocuronium when used in general anesthesia in clinical settings.

1. Methods

4.1. Study design

This was an active-controlled trial, in which a parallel group comparison of a novel rocuronium formulation and the traditional rocuronium formulation was conducted. Both formulations were used within approved indications (legal use). The two formulations were allocated in a random, open-label fashion, but the research team members evaluating the primary outcome were blinded to group allocation.

4.2. Sample size and its rationale

4.2.1. Sample size: Researchers’ university: 150 cases; total: 150 cases

4.2.2. Rationale: From the results of previous and pilot studies, the withdrawal response incidence in comparison groups was assumed to be 70% and the expected withdrawal response incidence in the study drug group is 45%. Based on Fisher’s exact test, with an assumed significance level of 2.5% (one-sided) and a power of 80%, the sample size was calculated to be 69 in each group, with a total of 138 people.

Considering drop-outs, we determined the sample size as 150 subjects in this study.

4.3. Methods

4.3.1. Samples/information used

Of the patients who underwent scheduled surgery under general anesthesia, patients/guardians from whom written consent for participation in this clinical study was obtained and those who were between the ages of 6 months and 65 years on the day consent was obtained were accepted as subjects, with no distinction by sex.

Patients excluded due to safety concerns:

• Patients with myopathy

• Patients with a history of hypersensitivity to rocuronium

• Patients with a history of hypersensitivity to both propofol and thiopental

• Patients with decreased upper limb muscle strength

• Obese patients (BMI ≥30)

4.3.2. Endpoints

Primary endpoint:

The primary endpoint was presence or absence of a withdrawal response after administration of the drugs. Scores from 2 to 4 points on the scale of Ahmad et al., that is, when movement of the arms is seen, were defined as withdrawal response^1^. A score of 1 on Ahmad’s scale, that is, absence of movement, was defined as no withdrawal response.

Secondary endpoints

• Magnitude of withdrawal response assessed using the scale of Ahmad et al.

• Blood pressure before and after drug administration

• Change in heart rate before and after drug administration

4.3.3. Observation and test items

Drug administration method

After entering the operation room, the subjects’ vital signs were monitored, the same as during regular general anesthesia, using an electrocardiograph, pulse oximeter, neuromuscular monitor, and sphygmomanometer.

Anesthesia was induced with intravenous administration of propofol (1-2 mg/kg body weight) or thiopental (3-5 mg/kg body weight). In cases in which standard induction was difficult, anesthesia was induced with inhalation of the anesthetic gas sevoflurane (mixture of 5% concentration in respiratory gas). Loss of consciousness was confirmed by disappearance of the patient’s eyelash reflex, following which the study was commenced. The rocuronium formulation was administered at the dose of 0.9 mg/kg body weight. In the traditional formation group, traditional formula rocuronium was administered, and the novel formula rocuronium was administered in the novel formation group.

Observation of physical changes

The parameters observed were withdrawal response of the arm in which the infusion needle was inserted and changes in heart rate and blood pressure. The arm observations were started just before the administration of rocuronium and made for 3 minutes after its administration. The upper body was imaged with a video camera centered on the arm with the infusion needle, and a research member blinded to the drug content evaluated the withdrawal response as seen in the video camera images and scored it according to its magnitude. The evaluations were done by the same researcher throughout the study to avoid inter-rater bias. Criteria used in previous published reports on vascular pain due to rocuronium injection were employed in the scoring, with a score of 2 or more taken to indicate the presence of a withdrawal response. For the changes in heart rate and blood pressure, the values just before and for 3 minutes after administration were compared with reference to the vital sign monitor records. Observation of the study subjects ended at the point when the 3-minute observations were completed.

Data collection items

The following data items were collected in this study.

• Subject characteristics: Sex, date of birth, height (cm), weight (kg), date consent was obtained, legal representative, primary disease leading to surgery, history of drug hypersensitivity.

• Evaluation at anesthesia: Administered drugs (traditional formation rocuronium, novel formation rocuronium), dosage, administration start date, presence of the arm withdrawal response and magnitude of the response (as evaluated by the blinded research member), heart rate (just before and 3 minutes after administration), systolic and diastolic blood pressure (just before and 3 minutes after administration), TOF ratio according to the muscle relaxation monitor (just before and 3 minutes after administration).

• Adverse events: Type of event, date of occurrence, seriousness, whether there was a causative association, outcome, date outcome was confirmed.

• Drop out information: Day of discontinuation, reason for discontinuation.

4.3.4. Statistical analysis method

The population to be analyzed was taken to be the full analysis set using the assigned treatment group in accordance with the principle of intention-to-treat. Fisher’s exact test was performed for the primary outcome of whether or not there was a withdrawal response. Mantel’s trend test was performed for the secondary outcome of the magnitude of the withdrawal response. Paired t-tests were performed for changes in blood pressure and heart rate before and after drug administration.

For the above analysis method, the details are described in the statistical analysis plan specified at the time of unblinding. However, other statistical method would be used in case that adjusted analysis by using participants’ age or other factors would be preferable.

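### Fisher's exact test for the primary outcome leaves part of the allowed 2.5% unused; Boschloo's exact test on the same endpoint and sample size adds 1.7 to 4.4 points of power at no cost

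*Protocol*

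**What the plan says.** The primary endpoint (protocol 4.3.2) is presence or absence of withdrawal. Scores 2 to 4, "when movement of the arms is seen, were defined as withdrawal response", count as a response, and score 1 is no movement. Section 4.3.3 repeats the cut, "with a score of 2 or more taken to indicate the presence of a withdrawal response". For the analysis, 4.3.4 states that Fisher's "exact test was performed for the primary outcome of whether or not there was a withdrawal response".

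Section 4.2.2 sizes the trial for this endpoint and this test. It assumes incidences of 70% with the existing formulation and 45% with the new one, "with an assumed significance level of 2.5% (one-sided) and a power of 80" per cent, and concludes that "the sample size was calculated to be 69 in each group, with a total of 138 people". Enrolment is raised to 150 to allow for drop-outs, with no drop-out rate given.

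The magnitude of the response on the full 4-point scale is a named secondary endpoint, tested with Mantel's trend test.

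**The concern.** Fisher's test fixes both margins of the 2×2 table, which this design does not do: only the group sizes are fixed. With few possible p-values under that conditioning, the test often cannot get close to the allowed error rate. The protocol permits 2.5% one-sided, and whatever the test leaves unused is lost power. An exact test that does not condition on the total number of responders can use more of the 2.5% and still guarantee it.

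The confirmatory result rests on this one test. At 69 per group, the number for which the trial was sized, Fisher's test reaches the 80% target with almost nothing to spare, so a few points matter if drop-outs use up the allowance. The test is named in the protocol itself, so the choice is not merely a detail left to the statistical analysis plan.

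**Working it through.** **Inputs (protocol 4.2.2 and 4.3.4).** Incidences 70% and 45%; one-sided 2.5%; 69 per group from the calculation; 75 per group from 150 / 2, assuming equal groups and no drop-outs.

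**Formulas.** Let x and y be the numbers of responders on the existing and the new formulation, with n per group.

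- Fisher one-sided p-value: P(X ≥ x | x + y), from the hypergeometric distribution with 2n subjects, x + y responders and n drawn. Reject if p ≤ 0.025.
- Power: the sum of Bin(x; n, 0.70) × Bin(y; n, 0.45) over all rejected tables.
- True size: the maximum over a common incidence π of the sum of Bin(x; n, π) × Bin(y; n, π) over the rejected tables.
- Boschloo's test: use Fisher's p-value as the test statistic and reject if p ≤ c, where c is the largest cut-off whose true size, computed as above, stays at or below 0.025.

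Fisher's test is the case c = 0.025, and its true size is already at or below 0.025, so c for Boschloo's test is never smaller. Every table that Fisher rejects is also rejected by Boschloo. That is why Boschloo's test cannot have less power.

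**Step 1: reproduce the plan's figure.** Exact Fisher power is 79.7% at 68 per group and 80.4% at 69. The stated 69 per group is confirmed.

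**Step 2: compare the two exact tests on the same endpoint.**

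| n per group | Test | True maximum size | Power |
|---|---|---|---|
| 69 | Fisher | 1.68% | 80.4% |
| 69 | Boschloo (c = 0.0344) | 2.49% | 84.8% |
| 75 | Fisher | 2.04% | 85.7% |
| 75 | Boschloo (c = 0.0341) | 2.49% | 87.4% |

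Gain at 69: 84.8 − 80.4 = 4.4 points. Gain at 75: 87.4 − 85.7 = 1.7 points.

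**Step 3: what the full score would add or lose.** The protocol gives no distribution over scores 2, 3 and 4, so this step rests on assumptions. Five control splits of the 70% who move were simulated: even, 60/30/10, 80/15/5, 25/50/25 and 20/30/50. The test is a tie-corrected Wilcoxon at one-sided 2.5%, and the fair comparator is Boschloo's test.

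- *Same odds ratio along the whole scale*, (0.70/0.30) / (0.45/0.55) = 2.85: Wilcoxon power at 69 per group is 88.5% to 91.6%. Against 84.8% that is +3.7 to +6.8, or about +4 to +7 points.
- *Drug changes only whether patients move, not how much*: Wilcoxon power at 69 per group is 77.0% to 80.7%. Against 84.8% that is −7.8 to −4.1, or about −8 to −4 points.

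Gain and loss are of similar size, and nothing in the protocol shows which pattern to expect.

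**The case against.** The strongest defence is that the plan is consistent. The stated primary outcome, the endpoint definition, the test and the sample size all concern the same any-movement event. The calculation is right for Fisher's test, 150 rather than 138 are to be enrolled, and a conservative test does not inflate false positives. Fisher's test is also familiar to readers. All of this stands, and it is why the point is an improvement and not an error. It gives no reason to prefer Fisher's test, because Boschloo's keeps the same endpoint and the same guarantee.

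A reader might go further and infer that cutting the score at 2 is itself the fault: the objective asks whether "injection pain associated with induction of anesthesia is milder when using a new rocuronium formulation than when using Eslax", so a primary test blind to severity among those who move would miss the question and lose 8 to 11 points of power. The documents do not support that.

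- The 8 to 11 points hold only at 69 per group, only under an assumed common odds ratio and assumed score splits, and only against Fisher's test. About 4.4 of them are Fisher's conservatism, recoverable without changing the endpoint.
- The cut is a natural zero, movement against no movement, and the protocol names presence or absence as the primary outcome directly after stating the objective.
- Severity is not ignored, since magnitude is a prespecified secondary endpoint with its own test.
- A test over all four scores would mix movers with non-movers, so it would not isolate severity among movers either.

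It remains true that the primary test does not respond to severity among those who move. That is a design choice the sponsor may make.

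**Conclusion.** The point holds as a free improvement. Under the protocol's own assumptions, Fisher's test uses at most 1.7% of the allowed 2.5% at 69 per group, and 2.0% at 75. Boschloo's test on the same data gains 4.4 points of power at 69 and 1.7 at 75. These are exact calculations that need only the stated incidences, level and group sizes; no assumption about scores 2 to 4 enters. Which gain applies depends on drop-out, for which no rate is stated, so both figures should be read together.

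The trial is not underpowered by its own plan. The 69 per group is correct and remains sufficient, and it would be wrong to say that there is no margin, because Fisher's test has 85.7% power if all 150 are analysed in equal groups. Replacing the primary endpoint with the 4-point score is an optional trade-off that can go either way.

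**What to change.** In protocol 4.3.4, and in the statistical analysis plan to match, replace Fisher's exact test for the primary outcome with Boschloo's exact unconditional test, and state there that it is one-sided at 2.5%. Leave the endpoint in 4.3.2, the cut at score 2, the secondary analysis of magnitude and the sample size as they are. In 4.2.2, keep the calculation and add that it was made for Fisher's test, so that power under the planned test is at least as high.

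The change must be fixed before unblinding. If group allocation has already been linked to the scores, Fisher's test should stay as the primary test.

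The cost is an amendment to the wording and software that offers the test. No data, patients, readers or staff are added. Should the sponsor wish to consider the full score as primary, that would be a change to the primary endpoint of a registered and ethics-approved trial. It would need its own justification, including an expected distribution over scores 2 to 4, and it is not needed to resolve this point.

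### The only test named for blood pressure and heart rate is a paired before/after t-test, which does not compare the two formulations

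*Protocol*

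**What the plan says.** Protocol section 4.1 describes "a parallel group comparison of a novel rocuronium formulation and the traditional rocuronium formulation was conducted", with random allocation. Section 1 asks whether "injection pain associated with induction of anesthesia is milder when using a new rocuronium formulation than when using Eslax", and under that objective states: "The secondary outcomes are the magnitude of the withdrawal response and changes in blood pressure and heart rate before and after injection of the drugs". It also explains why haemodynamics matter: irritation on injection can be a problem "when heart rate and blood pressure increase as a consequence". Section 4.3.2 lists three secondary endpoints: magnitude of the withdrawal response, blood pressure, and heart rate.

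Section 4.3.4 analyses the "full analysis set using the assigned treatment group in accordance with the principle of intention-to-treat". It assigns Fisher's exact test to the primary outcome, and for the graded response "Mantel’s trend test was performed for the secondary outcome of the magnitude of the withdrawal response". For the other two secondary endpoints it says: "Paired t-tests were performed for changes in blood pressure and heart rate before and after drug administration". Section 4.3.3 describes the haemodynamic comparison in the same way: "the values just before and for 3 minutes after administration were compared with reference to the vital sign monitor records".

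Two further clauses of section 4.3.4 bear on this. Details of the named methods are left to a statistical analysis plan fixed at unblinding. A different method may be used if adjustment for age or other factors is thought preferable.

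**The concern.** Each patient receives one formulation, so the only pairing available is before and after within a patient. A paired t-test asks whether the mean within-patient change is zero. It does not ask whether that change differs between formulations.

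The change over the three minutes is also not a pure injection effect. Induction with propofol, thiopental or sevoflurane comes just before rocuronium (section 4.3.3), and its evolving effect is part of every before/after difference. Only the concurrent arm can separate that from the effect of the formulation.

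At stake is whether these two endpoints can contribute to the comparative question. With the named test alone, a reader gets either no comparison or an informal one, made by setting the result in one arm beside the result in the other.

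**Working it through.** **1. The plan's own figure.** Section 4.2.2 gives 69 per group for 70% against 45%, Fisher's exact test, one-sided 2.5%, 80% power. Enumerating both binomial distributions gives exact power of 79.7% at 68 per group and 80.4% at 69, so 69 is confirmed. The plan gives no figure for blood pressure or heart rate.

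**2. What each named test compares.**

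| Outcome | Named test | Compares formulations? |
|---|---|---|
| Withdrawal, yes/no | Fisher's exact | Yes |
| Withdrawal, magnitude | Mantel trend | Yes |
| Blood pressure, heart rate | Paired t, before vs after | No |

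With D the within-patient change, the paired statistic is mean(D) / (SD(D)/√n). Treatment group does not appear in it. Run per arm, it tests each arm's mean change against zero. Pooled, it tests the overall mean change against zero.

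**3. Side-by-side reading (an assumption, not a protocol rule).** Inputs: 150 patients (section 4.2.1), taken as 75 per arm on assumed 1:1 allocation; two-sided 5%; the same true change in both arms, d, in SDs of the change. The protocol gives no mean change or SD, so a range is shown.

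- Power of one paired test: π = P(|T| > t critical), with T noncentral t on 74 df and noncentrality d√75. For d = 0.2 the noncentrality is 0.2 × 8.66 = 1.73.
- Chance that exactly one arm is significant: 2π(1 − π).

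| d | π | 2π(1 − π) |
|---|---|---|
| 0 | 0.050 | 9.5% |
| 0.10 | 0.137 | 24% |
| 0.20 | 0.401 | 48% |
| 0.23 | 0.494 | 50% |
| 0.30 | 0.727 | 40% |
| 0.40 | 0.928 | 13% |
| 0.50 | 0.990 | 2% |

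A direct between-arm test would be falsely significant 5% of the time at every d. With 69 per arm the pattern is the same: 9.5% at 0, 23% at 0.1, 47% at 0.2, 50% at 0.25, 43% at 0.3 and 17% at 0.4.

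At the bottom of the table the failure changes. Both arms are significant in π² of trials, 86% at d = 0.4 and 98% at d = 0.5, and this says nothing about which formulation changes haemodynamics less.

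**4. What a between-arm comparison could detect.** At 80% power and two-sided 5%, the detectable difference in mean change is (1.960 + 0.842) × √(2/n) SDs: 0.46 SD with 75 per arm and 0.48 SD with 69.

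**The case against.** The strongest reply is textual. The endpoints are worded as before/after quantities, and a paired t-test fits that wording. No sentence says that blood pressure or heart rate will be compared between groups; that requirement comes from the objective and the design. The analysis plan, not seen here, may contain such a comparison, and the adjustment clause already permits an ANCOVA with age. Analysis is by assigned group, so results by arm would be available.

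Part of this stands. It would go too far to infer that no between-arm comparison will be made, or that randomisation is thrown away for these endpoints. The documents leave room for a comparison. They do not commit to one: the plan is to supply details of the methods already named, and the adjustment clause is conditional and concerns covariates. The before/after wording defines the variable measured in each patient; the objective and design call for comparing it across arms.

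A reader might also infer that the trial intends to claim a haemodynamic advantage when one arm is significant and the other is not. The protocol states no such rule, and does not say whether the tests are per arm or pooled. The percentages above therefore describe a possible misreading. They depend heavily on d and fall below 5% at 0.5 SD. Discordance that favours the new formulation is only half of the total, π(1 − π), at most 25%, against 2.5% in that direction for a valid test.

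**Conclusion.** The point holds: the one test named for blood pressure and heart rate cannot compare the formulations, and nothing else in the protocol commits to a test that does. This follows from the form of the test and the parallel-group design, and needs no numerical assumption.

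The error rates are conditional on per-arm tests read side by side, 75 per arm, two-sided 5%, equal true changes and normally distributed changes. Under those conditions the chance that exactly one arm is significant runs from 9.5% at no change, through a peak of about 50% near 0.23 SD, to 2% at 0.5 SD. The documents do not show where in that range this trial lies.

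The change should be made, but this is not a flaw that threatens the trial. Only two secondary endpoints are affected. The primary Fisher test, the sample size and the trend test on magnitude are untouched.

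**What to change.** In protocol section 4.3.4, replace the paired t-tests with a between-arm comparison by assigned group for heart rate, systolic pressure and diastolic pressure: ANCOVA of the post-injection value on treatment, with the pre-injection value as covariate. Report the adjusted mean difference with its 95% confidence interval. Keep within-arm before/after changes as descriptive statistics only.

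Age may be added under the existing adjustment clause. If it is, its functional form should be stated, because eligibility runs from 6 months to 65 years. A two-sample comparison of change would also cure the defect; ANCOVA is suggested because it uses the pre-injection value directly.

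The cost is one sentence in section 4.3.4 and matching text in the analysis plan, settled before unblinding. Section 4.3.3 already collects the pre-injection and 3-minute values and date of birth, so no patients or measurements are added.
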